#### Extubation failure in the first 72 h after extubation

This the primary outcome for the development of APEX. Extubation failure is defined by one or more of the following criteria: (a) FiO_2_ > 0.5 to maintain SpO_2_ > 88% or PaO_2_ > 45 mmHg (for 2 consecutive hours); (b) PaCO_2_ > 55–60 mmHg with a pH < 7.25, in two consecutive blood gases done at least 1 h apart; (c) one episode of apnea requiring positive pressure ventilation with bag and mask; (d) Multiple episodes of apnea (≥ 6 episodes/6 h). This information will be collected prospectively from the nursing flow chart and blood gas records.

#### Extubation failure between 72 h and 14 days after extubation

Following the 72-h period after extubation, infants are monitored for presence of extubation failure criteria (as described above) until 14 days post-extubation.

#### Reintubation

This is a secondary outcome measure and is recorded at any time point from extubation until NICU discharge. The timing and reasons for reintubation are collected in detail since the decision to re-intubate is made by the responsible physician. Therefore, the indications for reintubation may differ from the criteria defining extubation failure.

*III. Data analysis.*

The analysis will be developed in 2 phases. Phase 1 will identify and evaluate cardiorespiratory features (metrics or patterns) that differ in infants who succeed/fail extubation. Phase II will use machine learning methods to determine the optimal combination of these features for the derivation of APEX.

### Phase I: Cardiorespiratory features

All signals will be exported to MATLAB™ (The MathWorks, Inc.) format for the following analyses:

*A)*
*Respiratory Signal Analysis.* AUREA will be used to describe respiratory activity in terms of a series of metrics that characterize the amplitude, frequency and phase information of the RIP signals on a sample-by-sample basis [52]. These metrics are computed automatically, provide quantitative measures of the respiratory activity and include:
*Instantaneous respiratory frequency (f*
_*max*_
*):* is the frequency in the respiratory band with the most power between 0.4 and 2.0 Hz. [57] It is estimated by passing the RIP signal through a bank of digital, band-pass filters; the central frequency of the filter with the highest output power at each time defines *f*
_*max*_
*.* This yields a sample-by-sample estimate with an accuracy of 0.1 Hz, or half the filter pass-band (0.2 Hz). Note that because we use symmetric, two-sided filters, there is no time delay in estimating *f*
_*max*_
*.*

*RMS metric:* extracts the amplitude information of the respiratory signals, and is defined as the sum of the root mean square (RMS) values for the ribcage (RCG) and abdomen (ABD) RIP signals.
*Pause metric:* is based on the power of regular breathing in either RCG or ABD. Pauses are defined by a lack of respiratory effort, so the RIP signals are expected to have low relative power in the regular breathing band (0.4–2.0 Hz). The pause metric is defined as the ratio of power in the regular breathing band for a short window to the median regular breathing power for the entire record. This metric is close to 1 during regular breathing and lower during pauses.
*Movement artifact metric:* defined separately for ABD and RCG, compares the power in the movement artifact band (i.e., 0–0.4 Hz) to that in the regular breathing band. It is calculated using the outputs of a filter bank spanning the frequencies 0–2 Hz; each filter has a 0.2 Hz bandwidth. This metric will be close to +1 during regular breathing and shift towards −1 during movement artifacts.
*Thoraco-abdominal asynchrony metric:* estimates the phase between RC and AB using selectively filtered RIP signals to improve the signal-to-noise ratio. The filtered signals are then converted to binary signals and an exclusive-OR signal is computed, representing the phase relation between RC and AB at each sample [58]. Averaging the resulting signal over a window length *N*
_*A*_ yields an asynchrony metric proportional to the phase shift.

Once the metrics are computed, AUREA then applies k-means clustering to these metrics to assign each time sample of the RIP signals to one of 5 respiratory patterns (also illustrated on Fig. 3):Pause (PAU)Synchronous-breathing (SYB)Asynchronous-breathing (ASB)Movement artifact (MVT)Unknown (UNK)

**Fig. 3 Fig3:**
[figure not shown]
Sample epochs of respiratory data from a preterm infant displaying the respiratory patterns detected automatically by AUREA. AUREA - Automated Unsupervised Respiratory Event Analysis system **a** Pause (PAU), **b** Movement artifact (MVT), **c** Asynchronous breathing (ASB) and **d** Synchronous breathing. Horizontal *dotted* lines indicate the center of each segment

The performance of AUREA’s assignment of respiratory patterns will be compared with results of an experienced manual scorer, and fine-tuned accordingly.

*B)*
*Heart Rate Analysis.* ECG signals acquired during the recording periods will be analyzed by first converting the ECG signal into a point process by identifying the maxima of the R wave. The resulting signal will then be low-pass filtered using the French-Holden algorithm [59] to generate a continuous HR signal. Instantaneous estimates of power in the: i) Very Low Frequency (VLF) = 0.01–0.04 Hz; (ii) Low Frequency (LF) = 0.04–0.2 Hz, and (iii) High Frequency (HF) = > 0.2 Hz bands will be determined by passing the continuous HR signal through a bank of band-pass filters with appropriate cut-offs. These filters will be implemented in the time domain as symmetric, two-sided finite impulse response filters, making it possible to track changes in HRV as a function of time with no delay.

*C)*
*Pulse Oximeter Analysis.* The PPG signal will be analyzed to detect movement artifacts using an algorithm that computes and removes a moving average of the larger quasi-periodic pulse components. The RMS of the residual will be close to zero for clean signals and higher during movement artifacts. This metric is faster and performs better than other methods that use higher order statistics [60, 61]. Oxygen saturation and Pulse Transit Time (PTT) will be computed for artifact-free segments. The PTT estimates the time elapsed between the R-wave of the ECG and the peripheral PPG pulse [62], and has been shown to be useful in the diagnosis of Obstructive Sleep Apnea Syndrome [63].

*D)*
*Stationarity.* Each metric is computed for each sample. The behavior of any given sample may vary randomly and/or as a function of time. This will likely occur during the 5-min period on endotracheal CPAP as the infant adapts to a sudden change on respiratory load. Consequently, the time course of each metric will be inspected to ensure that it is stationary. If not, we will first try to break the data set into shorter, quasi-stationary segments. Should this fail, the metric’s time-varying behavior will be described using time series analysis methods.

*E)*
*Feature Detection.* We will determine which statistical properties of these metrics describing cardiorespiratory activity are likely to be useful for predicting extubation readiness. To do so, subjects will be separated into two groups, defined by extubation failure or success, and the probability density (PDF) of each metric will be computed and compared. Differences in the variability of a metric will be revealed by changes in the shape of the PDFs; increased variability should result in a broader PDF while a decrease will result in a narrower PDF. In pilot studies, we found that the interquartile range was a useful feature to quantify variability. However, the shapes of the PDFs may suggest other statistics to use as features. The respiratory patterns generated by AUREA, along with the clinical variables collected, will be subjected to a similar analysis. The set of cardiorespiratory and clinical features with discriminative ability will be selected for use with machine learning methods to build the final predictor.

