### Sample size

The machine learning methods that will be used for this study have built-in mechanisms to guard against over-fitting the data (i.e., representing the training examples perfectly but having weak predictive power on new data). Consequently, traditional statistical approaches for determining sample size do not apply [65]. Therefore, sample size was estimated by applying a methodology proposed by Obuchowski and McClish and detailed by Zhou et al. [66, 67]. This method relies on estimating the prevalence of the disease of interest in the study population, estimating the variance of the receiver operating characteristics (ROC) curve based on a pilot study, and picking a required precision for the area under the curve (AUC). The prevalence of extubation failure was estimated conservatively to be 20%, based on both a review of the literature and the clinical collaborators’ experience. The variance in the AUC was then estimated by applying bootstrap methods to the data acquired in our pilot study. Using these values and an AUC precision of 0.1 led to an estimated sample size of 170 babies. This sample size would provide a minimum of 5 failure cases in each fold when performing 5-fold cross-validation, thereby ensuring a reliable measurement of generalization power [68]. Nevertheless, in the face of changing practice with the increasing use of HHHFNC post-extubation, and the uncertainty related to its impact on extubation failure rates in this population, the sample size was conservatively increased to 250 patients. As for the prospective validation of APEX, the sample size of 50 infants has been chosen large enough to demonstrate the anticipated benefits and feasibility of the predictor.

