### Statistical methods

#### Machine learning algorithms

The performance of the entire machine learning algorithm (described in ‘data analysis’ above) will be assessed using cross-validation, a standard approach that consists of splitting the data into several sub-sets (‘folds’) while ensuring that the distribution of the data in each subset is similar. Some subsets are used for feature selection and classifier training, while others are used for computing an unbiased estimate of the specificity and sensitivity of the classifiers. Each infant will be assigned to one subset of the data, such that data from the same infant will not be used both for training and testing. We will use stratified 5-fold cross-validation, which ensures that reliable estimates of the sensitivity, specificity, and variance of the predictors can be obtained. ROC curves reflecting the sensitivity and specificity trade-off will be produced and used to analytically determine the best trade-off from the point of view of clinical practice [57].

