The machine learning system will produce a binary prediction of whether a baby will succeed or fail extubation. However, for use in the clinical setting, a confidence measure in the classification would be necessary. To this end, we will use a method for estimating conditional probabilities for SVM, proposed by Platt [71], and efficiently implemented by Lin et al. [72]. This approach works on top of an existing support vector machine to produce an estimate of the probability that each example belongs to the class of interest. Our objective is to use these estimates to classify infants into 3 classes: (i) **FAILURE**: infants assigned to the failure group with high confidence; (ii) **SUCCESS**, infants assigned to the success group with high confidence; (iii) **UNCERTAIN**, infants assigned to either the success or fail groups with low confidence. Where the boundary should lie between high and low probability will depend upon the relative cost associated with a false negative (resulting in the extubation of an infant who will fail) versus that of a false positive (extending the period of ventilation for an infant who would otherwise be extubated). Given the nature of the experimental design (i.e. infants are only studied when deemed ready for extubation) we anticipate that the clinical implementation of our methods would involve delaying extubation for infants predicted to fail. We will evaluate performance based on two measures for the FAILURE class, the identification rate (IR) and the false discovery rate (FDR), defined as:$$ IR=\frac{NF_{fc}}{NF_T};\kern0.39em  FDR=\frac{NS_{fc}}{NS_{fc}+{NF}_{fc}} $$

*where NF*
_*T*_ = total number of failures

*NF*
_*fc*_ = number of failures assigned to FAILURE class

*NS*
_*fc*_ = number of successes assigned to FAILURE class.

Bootstrap methods will be applied to our data to estimate the threshold value that provides the largest value for IR with an acceptable FDR.

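### The protocol does not reconcile its Phase I outcome-based feature screen with selection inside training folds, and it tunes the IR/FDR threshold on the development data with no held-out step

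*Protocol article*

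**What the plan says.** Two parts of the protocol article bear on where features are chosen.

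- **Methods, III. Data analysis** sets out two phases in order. "Phase 1 will identify and evaluate cardiorespiratory features (metrics or patterns) that differ in infants who succeed/fail extubation". Phase II then combines those features by machine learning.
- **Phase I, E) Feature Detection** explains the screen: "subjects will be separated into two groups, defined by extubation failure or success, and the probability density (PDF) of each metric will be computed and" then set side by side for the two groups. The choice of summary statistic is left partly open: "However, the shapes of the PDFs may suggest other statistics to use as features". Respiratory patterns and clinical variables go through a similar analysis, and then "The set of cardiorespiratory and clinical features with discriminative ability will be selected for use with machine learning methods to build the final predictor". Folds and training subsets are not mentioned here.
- **Statistical methods, Machine learning algorithms** says: "The performance of the entire machine learning algorithm (described in ‘data analysis’ above) will be assessed using cross-validation". It continues: "Some subsets are used for feature selection and classifier training, while others are used for computing an unbiased estimate" of sensitivity and specificity. No infant contributes to both training and testing.

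On the operating point, the same section uses the study's own ROC curves to settle the trade-off. It then defines IR and FDR as the performance measures and says: "Bootstrap methods will be applied to our data to estimate the threshold value that provides the largest value for IR with an acceptable FDR". No nested or held-out step is described for that choice.

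Under IV. Prospective validation of APEX, 50 further infants are used for evaluation only, with the algorithm and its parameters fixed beforehand.

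**The concern.** Cross-validation gives an honest estimate only if every step that looks at the outcome is repeated without the test infants. Feature Detection looks at the outcome, and it reads as a stage completed before machine learning begins. Part of it is inspection of density shapes to devise new statistics, which is hard to repeat in each of five folds. If an infant's outcome has already helped to devise or choose the features, a further selection step inside the folds cannot undo that. Regularisation in the classifier does not help either, because it acts on fitting and not on features screened beforehand.

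The threshold raises the same issue on a smaller scale. Taking the cut-off with the largest IR at an acceptable FDR, and then quoting IR and FDR at that cut-off from the same infants, reports a maximum over noise.

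At stake is the credibility of the development estimates from 250 infants. At the planned 20% failure rate these contain about 50 failures, against about 10 in the validation set.

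**Working it through.** **1. The plan's own figures.** Sample size gives 20% failures, an AUC precision of 0.1, 170 infants and at least 5 failures per fold. The pilot AUC, its variance and the confidence level are not given, so 170 cannot be reproduced exactly. The binormal precision formula is

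n_fail = 1.96² × V / L², with V = 0.0099 × exp(−a²/2) × [(5a² + 8) + (a² + 8)/R], a = 1.414 × z(AUC), R = 4, L = 0.1, and N = n_fail / 0.20.

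| Assumed AUC | n_fail | N |
|---|---|---|
| 0.70 | 38 | 190 |
| 0.75 | 36 | 180 |
| 0.80 | 33 | 165 |
| 0.85 | 28 | 140 |
| 0.90 | 21 | 105 |

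So 170 is plausible. Failures per fold are 170 × 0.20 / 5 = 6.8 and 250 × 0.20 / 5 = 10, both consistent with the stated minimum. The point does not turn on these figures.

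**2. How many candidates?** The article gives no count. Table 2 lists roughly 36 clinical items known by the time of extubation. Phase I lists about 16 signal quantities: 6 AUREA metrics (counting the movement metric twice), 5 respiratory patterns, 3 heart-rate bands, oxygen saturation and pulse transit time. That is about 36 + 16 = 52, before several statistics per metric or two recording periods. The simulations use 20, 50 and 100.

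**3. Effect of where screening is done.** There were 100 simulated data sets per setting, with 20% failures and stratified 5-fold cross-validation. The top 10 features by t statistic were kept, and a regularised linear classifier stood in for the SVM.

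| N | Candidates | True signal | AUC, screened once on all infants | AUC, screened in training folds | AUC, new data | Once minus in-fold |
|---|---|---|---|---|---|---|
| 170 | 20 | none | 0.599 | 0.498 | 0.501 | 0.10 |
| 170 | 50 | none | 0.686 | 0.484 | 0.500 | 0.20 |
| 170 | 100 | none | 0.744 | 0.496 | 0.500 | 0.25 |
| 250 | 20 | none | 0.576 | 0.494 | 0.499 | 0.08 |
| 250 | 50 | none | 0.659 | 0.486 | 0.496 | 0.17 |
| 250 | 100 | none | 0.707 | 0.491 | 0.500 | 0.22 |
| 250 | 50 | 5 features, 0.5 SD | 0.795 | 0.721 | 0.730 | 0.07 |
| 250 | 100 | 5 features, 0.5 SD | 0.810 | 0.704 | 0.719 | 0.11 |

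In-fold screening tracks new data; one-off screening does not. A separate simulation at N = 250, keeping 17 noise features (the number combined in the pilot), gave AUC 0.65, 0.72 and 0.77 for 50, 100 and 200 candidates, against 0.50 in-fold.

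**4. Effect of tuning the threshold on the reported data.** Features were screened in-fold, the threshold was set for the largest IR with FDR below 0.5 on the out-of-fold scores, and it was then applied to new data (N = 250, 5 true features):

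- 50 candidates: IR 0.260 against 0.218 (0.04 too high); FDR 0.438 against 0.471 (0.03 too low).
- 100 candidates: IR 0.217 against 0.176 (0.04 too high); FDR 0.438 against 0.466 (0.03 too low).

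The new-data figures come from a model refitted on all 250 infants, so a small part of the gap may reflect the refit and not the tuning.

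**5. What the validation set can carry.** 50 × 0.20 = 10 expected failures. If 8 of 10 are identified, the exact 95% confidence interval for IR is 0.44 to 0.97.

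**The case against.** A reader might infer that the protocol selects features on the whole data set and therefore plainly breaks its own promise. The text does not say so. Feature Detection speaks of subjects without saying all 250, or before the folds are formed. Statistical methods cross-validates the entire algorithm and points back to data analysis, the heading that covers both phases. It also places feature selection in the training subsets. On that reading the safeguard is already in the plan. This part of the objection stands, so a one-off screen on all infants can be put only as a condition.

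A reader might also infer that threshold tuning alone distorts IR greatly. In one simulated setting IR was 0.44 with whole-sample screening and 0.07 with in-fold screening, but that gap mainly reflects leaked features. The tuning effect by itself is about 0.04. The claim of an unbiased estimate is made for sensitivity and specificity in held-out subsets, not for IR and FDR at the tuned cut-off, and AUC does not depend on the cut-off.

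The locked validation in 50 new infants is free of both problems, and the targets of IR 0.8 and FDR below 0.5 are stated there. Nor does the article say that the development figures decide which algorithm is frozen. The sentence under Sample size that "The machine learning methods that will be used for this study have built-in mechanisms to guard against over-fitting the data" justifies the sample-size method; it does not claim protection against screening outside the folds.

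Finally, a journal article may leave details of nesting to a fuller document. That is fair for tuning and probability scaling. It does not remove the tension between two passages that the article does contain.

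**Conclusion.** The concern holds as an unreconciled inconsistency plus a modest threshold problem; it does not show that features are selected on all infants.

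- **Screening.** The phase order and the open-ended inspection of densities suggest a one-off screen, while Statistical methods describes in-fold selection. If the former is what is done, cross-validated sensitivity, specificity and AUC are too favourable. The AUC excess was 0.08 to 0.25 with noise features only and 0.07 to 0.11 with five moderately informative ones. If the latter is done for all of Phase I, there is no upward bias from this source and only the wording needs to change.
- **Threshold.** As written, the cut-off is set on the development data with no held-out step. IR and FDR quoted from those data would be slightly optimistic, about 0.04 and 0.03 in the settings tried.

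The sizes rest on assumed candidate counts, independent normal features, t-statistic ranking and a linear classifier. The pilot results reported in the article suggest some real signal, so the noise-only figures are an upper illustration, not a forecast. The 50-infant validation is a sound independent check, but with about 10 failures it is too imprecise to replace an honest development estimate.

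**What to change.** 1. Reconcile Data analysis and Feature Detection with Statistical methods. State that the outcome-based part of Phase I, including any statistic suggested by the densities, is redone within each training fold by a rule that can be executed without the test infants. Label whole-sample density comparisons as descriptive only.
2. Choose the operating point and the IR/FDR threshold within the training folds, apply them unchanged to the outer test fold, and report development IR, FDR, sensitivity, specificity and AUC from outer test folds only.
3. Alternatively for the threshold, report threshold-based performance only from the locked 50-infant validation, with confidence intervals and a note that about 10 failures are expected.

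The cost is wording, analysis code, more computing time and probably a less favourable development estimate. No additional infants or data are needed. Replacing visual inspection with a repeatable rule gives up some exploratory freedom in the predictor, though not in the descriptive analysis.

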### Phase II: Machine learning

The machine learning phase will examine the hypothesis that subjects ready for extubation can be differentiated from those who are not by using a classifier that combines clinical variables with the features computed in Phase I.

For classification, infants will be assigned to either the SUCCESS or FAILURE groups depending on the primary outcome, extubation failure or success. We will then use discriminative classification algorithms (e.g. SVM [54] and Adaboost [64]) to construct classifiers for risk assessment. SVM is a powerful classification method, which takes existing labeled examples and constructs a non-linear decision boundary providing a class separation. New examples are then classified by comparing them to this boundary. SVM relies on two important insights: the boundary can be defined by the examples that are closest to it (called support vectors) and any new instance can be classified by comparing it to the support vectors. This implicit way of defining the decision boundary permits the use of large numbers of attributes, and the discovery of non-linear relationships between them (rather than simple logical relationships such as “AND” and “OR”). The algorithms to be used provide non-linear classification boundaries as well as a measure of uncertainty in the labeling of each example (expressed as a “margin” between the example and the classification boundary). Unlike other learning algorithms that produce non-linear classifiers, such as neural networks, these algorithms are known to work well with limited numbers of examples, as is the case for our data, and to be very robust to noise in the input features.

*IV. Prospective validation of APEX.*

The development of APEX as described above will use a variety of specialized software tools. These provide the flexibility necessary for exploratory research but may not be suitable for clinical use. Therefore, we will develop an integrated software system that will perform all the data acquisition, signal analysis, and classification operations needed to predict extubation outcome with a user-friendly interface suitable for medical personnel in the NICU. Prototypes of the package will be developed and tested using MATLAB’s interactive environment, which supports all the needed algorithms and provides a complete set of tools for graphical interface development. Once a prototype is available, its clarity and usability will be assessed by recruiting clinicians from the NICUs (neonatologists, respiratory technicians) to test the package in a simulated setting and provide feedback. Once the package is finalized, the MATLAB compiler will be used to generate a stand-alone application that will be installed on the data acquisition machines.

The performance of APEX will then be validated in a prospective study of an additional 50 preterm infants. These will be used only to evaluate the performance of the predictor in the clinical setting. Moreover, the APEX classification algorithm and parameters will be pre-specified and used for all infants. Patient recruitment, acquisition, and follow-up will be the same as for the original study. However, immediately following completion of the cardiorespiratory recordings, APEX will carry out the signal analysis and classification computations to assign the infant to FAILURE, SUCCESS, or UNCERTAIN groups (see ‘Statistical methods’ below). This APEX classification will not be available to the attending staff and so will not influence clinical care.

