The role of HRV and RV in predicting disease in newborn infants is not understood as well. However, it has become increasingly attractive over the past years, as recent evidence suggests that loss of HRV precedes the clinical presentation of neonatal sepsis [46]. The potential for cardiorespiratory variability measurements to predict extubation readiness has led our group to explore their usefulness in the extremely preterm population. The first evaluation was conducted as part of a retrospective analysis of respiratory data collected by Kamlin et al., whereby RV indices were computed during a 3-min SBT performed prior to extubation [35]. The combination of RV and clinical response to the SBT predicted successful extubation more accurately than either test alone [47]. However, the study used a pneumotachograph to measure respiration, a tool that has several limitations [48]. For those reasons, we conducted a pilot prospective observational study of 56 preterm infants (BW ≤1250 g) in which cardiorespiratory behavior was obtained from electrocardiogram (ECG) and respiratory inductive plethysmography (RIP) signals that captured respiratory movements from the ribcage and abdomen. Data were collected during 2 periods prior to extubation: a 60-min recording on low ventilatory support followed by a 3-min period on endotracheal CPAP. The primary outcome, extubation failure, was defined as the need for reintubation within 72 h from extubation. The study revealed that HRV was significantly lower in infants who failed their first extubation attempt [49]. In addition, both HRV and RV measures had perfect specificity and PPV, but limited sensitivity and NPV. Nevertheless, a major factor limiting the evaluation of RV was the need for manual, breath-by-breath analysis of the respiratory signals. Manual analysis of respiratory signals is expensive, time consuming, operator-dependent and prone to errors. To circumvent this problem, it became more attractive to use an automated, continuous analysis of respiratory behavior. One such example is AUREA, a robust Automated Unsupervised Respiratory Events Analysis system developed by members of our team [50]. AUREA uses uncalibrated RIP signals to compute a number of respiratory-related metrics that are then used to classify the infant’s respiratory patterns on a sample-by-sample basis. The method is fully automated, completely repeatable, standardized, and requires no human intervention. Importantly, it is more efficient than manual scoring (the most common method of analysis) and is not limited by intra- or inter-scorer variability [50].

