### Rationale

Both prolonged MV and the need for reintubation are associated with short- and long-term complications. Therefore, it is critical to determine the optimal timing for extubation to minimize the duration of MV while maximizing chances of success. There is promising evidence that analysis of cardiorespiratory signals can provide valuable information into the extubation readiness of extremely preterm infants. We therefore hypothesize that extubation readiness of preterm infants can be determined accurately by using machine learning methods to combine clinical variables along with novel, quantitative and automated measures of cardiorespiratory behavior.

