#### Prospective APEX validation

The predictive validity of APEX in the clinical context will be evaluated in two ways.

First, we will evaluate the accuracy with which infants are assigned to the high confidence SUCCESS and FAILURE groups by comparing the predicted and observed outcomes. We expect that infants will be assigned to these high-confidence groups with high accuracy. Second, the clinical utility of the approach will also depend on the benefits and costs associated with its potential impact on patient outcome. The **benefits** of using the method can be summarized in terms of the IR, the proportion of extubation failures that could potentially be prevented. The **costs** can be summarized in terms of the FDR, the proportional of infants incorrectly assigned to failure class. Our objectives are to obtain an IR of 0.8 and an FDR of less than 0.5. This would translate into reducing the extubation failure rate from an estimated 20% to less than 5%, at the cost of prolonging the ventilation of one infant for each extubation failure prevented.

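### As planned, only the combined classifier is evaluated, so a good result would not show that the cardiorespiratory signals add to the clinical variables already charted

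*Protocol article*

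**What the plan says.** The Rationale hypothesises that readiness can be determined accurately by "using machine learning methods to combine clinical variables along with novel, quantitative and automated measures of cardiorespiratory behavior". Phase I, item E (Feature Detection), compares the distribution of each metric between infants who succeed and infants who fail, treats the clinical variables similarly, and then pools them: "The set of cardiorespiratory and clinical features with discriminative ability will be selected for use with machine learning methods". Phase II builds "a classifier that combines clinical variables with the features computed in Phase I".

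Statistical methods assesses the whole algorithm by stratified 5-fold cross-validation with ROC curves, sensitivity and specificity. For the three-class output it adds: "We will evaluate performance based on two measures for the FAILURE class", namely IR and FDR. Prospective APEX validation first compares predicted with observed outcomes in the high-confidence SUCCESS and FAILURE groups, and then sets numerical aims: "Our objectives are to obtain an IR of 0.8 and an FDR of less than 0.5". Nothing in the article names a clinical-only model, a signals-only model or a difference between models as something to be estimated.

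**The concern.** The Background says that present decisions rest on judgement informed by blood gases, oxygen requirements and ventilator settings. The Rationale offers cardiorespiratory signal analysis as the source of new information. Table 2 lists those same charted items at the time of extubation, and the classifier may use them alongside the signals. If the combination predicts well, the credit could belong to the charted variables, to the signals or to both, and every planned measure would look the same in each case.

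At stake is what the study can conclude. The inductance bands, the 60-min recording, the 5-min endotracheal CPAP recording and the integrated bedside software are worth their burden only if the signals improve on data already in the chart. An accurate APEX would leave that open.

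**Working it through.** **1. What the targets measure.** IR is failures assigned to FAILURE divided by all failures. FDR is successes assigned to FAILURE divided by all infants assigned to FAILURE. Both depend on the final counts alone.

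- At the planned 20% failure rate (Sample size), 250 infants give 250 × 0.20 = 50 failures and 200 successes.
- IR 0.8 means 0.8 × 50 = 40 failures flagged. FDR below 0.5 then means fewer than 40 successes flagged.
- Failures not flagged are 10/250 = 4% of infants, in line with the article's aim of bringing 20% to below 5%. At the limit FDR = 0.5, one success is held back per failure flagged, which is also the article's figure.

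A clinical-only classifier with the same 40 and fewer than 40 would meet the same targets. ROC, sensitivity, specificity and group accuracy, computed for one model, have the same property.

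**2. Whether Phase I fills the gap.** It compares features one at a time between outcome groups. A signal feature can differ between groups because it tracks gestational age, weight or ventilator settings, and then contribute nothing once these are in the model. Phase I therefore shows marginal association and not added value.

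**3. What a paired comparison could show in development.** The article gives no clinical-only AUC and no correlation between scores, so these are assumptions: AUC 0.75 (clinical only), 0.82 (combined), binormal scores, correlation 0.3 to 0.85 within infant. By simulation with 50 failures and 200 successes, 95% half-width = 1.96 × SE and power ≈ Φ(0.07/SE − 1.96):

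| Score correlation | SE of difference | 95% half-width | 0.07/SE | Power |
|---|---|---|---|---|
| 0.3 | 0.044 | 0.086 | 1.59 | 36% |
| 0.5 | 0.037 | 0.073 | 1.89 | 47% |
| 0.7 | 0.030 | 0.059 | 2.33 | 65% |
| 0.85 | 0.022 | 0.043 | 3.18 | 89% |

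Closed-form check: Hanley-McNeil standard errors for the two AUCs are 0.042 and 0.038. SE = √(v₀ + v₁ − 2r√(v₀v₁)), with r the correlation of the two AUC estimates, runs from 0.048 (r = 0.3) to 0.022 (r = 0.85), a similar range.

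All of this treats the scores as fixed. Refitting and fold-to-fold variation would widen the intervals somewhat.

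**4. The same comparison in the validation set.** Fifty infants give about 50 × 0.20 = 10 failures. The SE is about 0.051 to 0.098, so the half-width is about 0.10 to 0.19 and power is Φ(1.37 − 1.96) = 28% at best and Φ(0.71 − 1.96) = 11% at worst. Only a descriptive result can come from that set.

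**The case against.** The strongest reply is that the hypothesis concerns the combination and nowhere promises to attribute its accuracy to the signals. A reference is also built in: every infant has already been judged ready by the physician, so failures correctly flagged are ones that judgement missed. Both statements are right. They mean that the plan answers its stated hypothesis. They do not show which inputs supply the gain, and the Rationale's case for recording signals depends on that.

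A second reply is that this is a condensed article and that a reduced-model analysis may stand in a fuller document. That is possible. But the article itself fixes the hypothesis, the measures and the numerical targets, all on the combined model.

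A reader might infer more than the article supports:

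- *That success is judged by IR and FDR alone.* ROC, sensitivity, specificity and accuracy of both high-confidence groups are also planned.
- *That the team has abandoned a comparison it once made.* The Background does report that "The combination of RV and clinical response to the SBT predicted successful extubation more accurately than either test alone", but that was a retrospective analysis of another dataset, and nothing in the article rules out such a comparison here.
- *That the bedside response to the CPAP period is a ready comparator.* Table 2 does not list it, no pass/fail rule is given, and oxygen requirement during the 5 minutes is not listed. A response derived from heart rate and SpO2 would overlap the Phase I signals.
- *That the cited 3-min breathing trial already does as well.* Its 97% sensitivity and 73% specificity for success, at 20% failure, give IR 0.73 and FDR 0.024/(0.024 + 0.146) = 0.14. They come from another cohort, and the Background also cites a later study with limited specificity and an audit showing no benefit from routine use. The figures illustrate that absolute targets do not establish improvement, and no more.

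**Conclusion.** The point holds for the planned analysis: evaluated alone and against absolute targets, the combined classifier cannot show that the signals add to the charted variables. It does not hold for the study as such, because the data needed are being collected and no stated claim is invalidated. Nor is there evidence in the article that the signals add nothing.

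The comparison would be informative in the 250 development infants as an estimate with an interval: half-width about 0.04 to 0.09 in AUC, and power about 36% to 89% for a gain of 0.07. Those figures rest on the assumed AUCs and correlations and on the 20% failure rate. This is an inexpensive improvement that widens what can be concluded, and not a fatal fault.

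**What to change.** Specify before results are seen:

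1. In the same stratified 5-fold splits, run the identical pipeline, feature selection in the training folds included, on clinical variables only. Use exactly the pre-extubation Table 2 variables offered to the combined model.
2. Report the paired difference, combined minus clinical-only, in AUC and in IR at the same FDR, with bootstrap intervals that resample infants and keep each infant's two scores together. Present it as an estimate and not as a powered test.
3. If the clinical-only model is also scored in the 50 validation infants, label the result descriptive.

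This needs no new infants, recordings or change in care. The cost is one further run of the pipeline plus the bootstrap, and the possibility that the result is less favourable to APEX.
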